## **2.4 Secondary Endpoints**

- Molecular response as efficacy end point.
- Progression free survival at 1 year after initiation and the end of CIK cell therapy.
- Overall survival will be assessed 1 year after initiation and the end of CIK cell therapy.

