## **3 Study Design**

This is a phase I/II study to investigate the feasibility, safety and efficacy of IL-15 activated CIK cells in patients with acute leukemia or MDS showing evidence of molecular relapse after allogeneic SCT.

- CIK cell infusions will be given with an interval of 4-6 weeks according to a dose escalation schedule in patients with impending relapse after allogeneic SCT. In presence of aGvHD  $\geq$  grade II, the next scheduled infusion will not be administered. CIK cell infusions will be administered until the patient reaches molecular remission, until a maximum of 8 infusions are reached or until the patient progresses, provided that patients develop no more than grade I aGvHD.

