**The following criteria lead to stop of additional CIK cell infusions; patients are remaining in the study:**

- Development of GVHD > Grade II
- Response to CIK cell therapy: If mixed chimerism was the reason for study eligibility, than the achievement of complete donor chimerism leads to the stop of further CIK cell infusions. If the inclusion into the study was favored by minimal residual disease detection, the achievement of MRD negativity leads to a stop of additional CIK cell infusions.

- Severe infections

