**The following criteria lead to withdrawal from study; patients will be followed up for one month:**

- Pregnancy of female patients
- Relapse of the underlying disease during CIK cell treatment requiring other treatment (e.g. systemic chemotherapy, second stem cell transplantation)

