## Analysis

A descriptive statistics will be performed at the end of the study. An intent-to-treat principle (ITT) or per-protocol analysis will be done.

To analyze the efficacy of CIK cell treatment following factors will be considered:

- Complete and partial molecular response
- rate and duration of complete/partial molecular response following CIK cell administration at the end of CIK cell infusions and after 1 year of first CIK cell infusion
- rate of and time to non response
- rate of and time to relapse with previous partial/complete response
- Progression-Free survival (PFS) and overall survival (OS)
- Cumulative incidences of: haematological relapse/progression, deaths without relapse/progression
- Cumulative incidence of aGVHD > grade II and extensive chronic GvHD
- Median and range for the number of CIK cell dose and for cumulative dose CIK cells/kg for all patients, children and adults

- Median and range for cumulative T cells/kg according donor type (MSD, MUD,MMFD) that patient requires in the study

Complete molecular response is defined as the molecular remission: the Minimal Residual Disease not detectable (MRD < 10^-6) and Mixed Chimerism MC < 1%.

Partial response is defined as no molecular remission but not haematological relapse. Non response is defined as haematological relapse without previous or complete response.

The median of PFS and OS time will be estimated. Kaplan-Meier estimates will be used to estimate PFS probability and OS probability. Log-rank test will be used as appropriate. For PFS will be considered as events: disease progression or relapse, death without relapse/progression and secondary neoplasm. For OS death from any cause will be considered an event.

Gray-Model will be used for cumulative incidences. Patients lost to follow-up without event will be censored at the date of their last follow up evaluation.

PFS, OS and cumulative incidences will be estimated after 1 year initiation of CIK cell therapy and after 1 year until the last CIK cell infusion.

If the data meet the necessary requirements, longitudinal analysis will be conducted to explore the improvement of hematologic and immune reconstitution of leucocyte, CD3-, CD4-, CD8-, CD56-, and CD14-positive cells until the first year after begin of the CIK cells therapy.

The dynamic of cytokine profile during cell infusion and tumor escape mechanisms following CIK cell infusion will exhibit in curves over the time.

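### PFS, OS and cumulative incidences are also set at 1 year after the last CIK infusion, a date fixed largely by the outcomes analysed, so those estimates are confounded by infusion interval and stopping reason

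*Protocol*

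**What the plan says.** Section 2.4 of the protocol lists "Progression free survival at 1 year after initiation and the end of CIK cell therapy" and states that "Overall survival will be assessed 1 year after initiation and the end of CIK cell therapy". The synopsis repeats both. The Analysis part of section 11 extends the pair of time points to cumulative incidences: all three are to be "estimated after 1 year initiation of CIK cell therapy and after 1 year until the last CIK cell infusion". The second half of that sentence is garbled, and no section states time zero.

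The date of the last infusion is decided as follows:
- Section 3 gives infusions "until the patient reaches molecular remission, until a maximum of 8 infusions are reached or until the patient progresses". Section 3.3 repeats this.
- Section 8.1 stops infusions, with the patient remaining in the study, on "Development of GVHD > Grade II", on severe infection and on response: complete donor chimerism for patients enrolled on mixed chimerism, and for those enrolled on MRD "the achievement of MRD negativity leads to a stop of additional CIK cell infusions".
- Section 8.1 withdraws patients for "Relapse of the underlying disease during CIK cell treatment requiring other treatment".

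Infusions are 4 to 6 weeks apart (section 3.1), and patients who stay in the study are observed for one year after the last one (section 3.3). Section 11 calls the study explorative and the analysis descriptive. It gives no landmark, no split by stopping reason and no rule for events that themselves end treatment.

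**The concern.** A time origin should be fixed before the outcome is known. Here the origin is a post-baseline date that in many patients is produced by the outcome. A patient who progresses during treatment had an infusion within the previous 4-6 weeks, so the clock starts just before the event. A patient whose disease is held for eight infusions has the whole treatment period removed. The end-of-therapy result therefore depends on the interval chosen within the permitted range and on the mix of stopping reasons, as well as on disease control. It is a named secondary endpoint, in a study meant to inform a larger one. A median, a 1-year probability or a log-rank test on this origin could be read as efficacy when part of it comes from the schedule.

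**Working it through.** The protocol gives no expected PFS, OS or cumulative incidence, so there is no figure of its own to reproduce on this point. Its exact confidence intervals for response do reproduce (n = 40, rate 0.4: 0.249 to 0.567, width 0.318) but do not bear on it.

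**From the text alone**
- Eight infusions span 7 intervals: 7 × 4 = 28 to 7 × 6 = 42 weeks.
- PFS from the last infusion for progression before the next infusion is due: at most one interval, 4 to 6 weeks.
- Example with 5-weekly infusions: patient A progresses at week 33, after infusions at weeks 0, 5, ..., 30. PFS is 33 weeks from the first infusion and 33 − 30 = 3 weeks from the last. Patient B stops after one infusion for GvHD and progresses at week 10: 10 weeks from either origin. Changing the origin reverses their order.

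**Size, under stated assumptions**

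Assumptions, none of them in the protocol: constant hazard with median m weeks; no effect of stopping on the hazard; a chance r at each of infusions 1 to 7 of stopping for a reason other than progression. From the protocol: interval d within 4-6 weeks, maximum of 8 infusions, stop at progression.

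Let S(52) = 2^(−52/m), q = 2^(−d/m) and g = (1 − r)q. The share of patients whose treatment is not ended by progression is

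A = r(1 − g^7)/(1 − g) + g^7.

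On-treatment progressors contribute 0 at one year from the last infusion. The others contribute S(52), because the hazard is constant. So 1-year PFS from the last infusion = A × S(52).

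Example, m = 26, d = 5, r = 0.08: q = 0.8752, g = 0.8052, g^7 = 0.2194, A = 0.08 × 0.7806/0.1948 + 0.2194 = 0.540, PFS = 0.540 × 0.25 = 0.135.

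| True median (weeks) | True 1-year PFS | r | A | 1-year PFS from last infusion | Median from last infusion (weeks) |
|---|---|---|---|---|---|
| 26 | 0.25 | 0 | 0.393 | 0.098 | 3.8 |
| 26 | 0.25 | 0.08 | 0.540 | 0.135 | 4.7 |
| 26 | 0.25 | 0.25 | 0.742 | 0.185 | 14.8 |
| 39 | 0.40 | 0 | 0.537 | 0.213 | 4.9 |
| 39 | 0.40 | 0.08 | 0.654 | 0.259 | 15.1 |
| 39 | 0.40 | 0.25 | 0.811 | 0.322 | 27.2 |

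At r = 0.25 the share stopping before the eighth infusion for a reason other than progression is A − g^7 = 0.742 − 0.053 = 69% (median 26) or 0.811 − 0.072 = 74% (median 39). That row is therefore a generous upper case.

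**Interval alone.** With true 1-year PFS 0.50 (m = 52) and r = 0, A = 2^(−28/52) = 0.689 at 4 weeks and 2^(−42/52) = 0.571 at 6 weeks. PFS from the last infusion is 0.34 or 0.29. Simulation with 400,000 patients per scenario gives the same values (0.343, 0.286).

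**Does the estimate still carry signal?** At 4 weeks with r = 0, true values of 0.30, 0.50 and 0.70 give 0.16, 0.34 and 0.58. Among patients who did not progress on treatment, the true value is returned.

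**Alternative reading: a readout date, with time counted from first infusion.** The readout is at week 0 + 52 = 52 after a single infusion, and at week 28 + 52 = 80 to 42 + 52 = 94 after eight.

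**The case against.** The strongest reply is that the protocol never states time zero. Being assessed one year after the end of therapy can mean a readout at the close of the observational year, with time still counted from the first infusion. On that reading the table above does not apply. This stands as far as it goes, but the readout then varies with outcome by up to 94 − 52 = 42 weeks and is still not a common 1-year estimate. A SAP could define time zero, but the protocol itself names the end-of-therapy time point as an endpoint.

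Several stronger readings are tempting and are not supported:
- A reader might infer that these results measure schedule and stopping reason and not efficacy. They do not measure only that: the estimate rises with true PFS, and in patients who stop for remission it describes off-treatment durability.
- A reader might apply the calculation equally to OS and GvHD. Only PFS was computed. Death after progression is not bounded by one interval.
- A reader might infer planned log-rank comparisons by donor type or by response on this origin. Section 11 says only that the test is used where appropriate, and donor type appears there only for cumulative T-cell dose.
- A reader might want every post-therapy summary removed. For GvHD, a window of fixed length after last exposure is useful: after eight infusions, one year from initiation leaves only 52 − 42 = 10 to 52 − 28 = 24 weeks after the last infusion.

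The study is also explorative, single-arm and descriptive, and the initiation-based analysis is planned. This limits the consequence to the second time point.

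**Conclusion.** The point holds in a limited form. Timed from the last infusion, PFS and relapse incidence are confounded by infusion interval and reason for stopping. For OS the same bound applies only to deaths during treatment. That on-treatment progressors have at most 4-6 weeks, and that up to 28-42 weeks are dropped for eight infusions, follows from the protocol alone. The size does not: it rests on constant hazards, 5-weekly infusions and non-progression stops of 0 to 25% per infusion. On those assumptions a true 1-year PFS of 25% appears as about 10-19%, and one of 40% as about 21-32%. The distortion is smaller where more patients stop for reasons other than progression.

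The calculation follows section 3, where progression ends infusions. Section 5.4 allows modified doses after progression, which would put the last infusion after the PFS event. The two passages must be reconciled.

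The estimates from initiation are free of this problem. It should be corrected, but it does not threaten the study's primary safety result.

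**What to change.** In the synopsis, section 2.4 and section 11:
- State the first infusion as time zero for PFS, OS and the cumulative incidences of relapse/progression and of death without relapse, and report them at 1 year.
- Do not use the last infusion as an efficacy origin or for log-rank tests.
- Report post-therapy outcomes descriptively by reason for stopping, for example duration of response from documented complete molecular response in patients who stopped for remission.
- GvHD within one year of the last infusion may stay as a descriptive safety summary, labelled as such.

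This is a wording change with no new visits or data. The cost is that the pooled end-of-therapy PFS and OS figure is no longer reported as an efficacy result. The change does not address a separate limit: patients withdrawn for relapse are followed for only 28 days or one month (sections 3.3 and 8.1), which restricts 1-year OS from either origin.

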## 13 Appendices

### APPENDIX 1

#### Glucksberg acute GvHD scores

##### Skin

- Stage 0: No rash
- Stage 1: Maculopapular rash <25% of body surface area
- Stage 2: Maculopapular rash on 25-50% of body surface area
- Stage 3: Generalized erythroderma
- Stage 4: Generalized erythroderma with bullous formation and desquamation

##### Liver

- Stage 0: Bilirubin <2 mg/dL
- Stage 1: Bilirubin 2-3 mg/dL
- Stage 2: Bilirubin 3.01-6 mg/dL
- Stage 3: Bilirubin 6.01-15.0 mg/dL
- Stage 4: Bilirubin >15 mg/dL

##### GI

- Stage 0: No diarrhea, or diarrhea <500 mL/day
- Stage 1: Diarrhea 500-999 mL/day
- Stage 2: Diarrhea 1000-1499 mL/day
- Stage 3: Diarrhea >1500 mL/day
- Stage 4: Severe abdominal pain, with or without ileus

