## **1.2 Differences between adult and pediatric patients with acute and chronic leukemia and with MDS**

Treatment and prognosis of patients with leukemia and MDS differs significantly between children and adolescents and adult patients. As a consequence the prognosis in childhood is by far better than in adulthood. In the medical community it is generally accepted that children are not small adults.

The physiology of children differs from that of adult individuals fundamentally. This is true on all aspects of metabolism. Children are tolerating all kind of drugs better than adult patients. Half-life time of drug excretion is different between children and adults. This is also true for example in the antibody immunotherapy. It could be shown in this field that also the response rate to the drug is different between children and adults; in this time in favor for adult patients.

This proves that leukemic blasts are frequently different between juvenile and adult leukemia cells. Regularly childhood leukemia and MDS is more susceptible for all kind of treatment. Therefore treatment schedules can be different and as a consequence for what is learned from treating adult patients only little is transferable to the treatment of children.

This is in particular true in the setting of allogeneic stem cell transplantation. In this field the differences in physiology of both patient groups is apparent. So is the rate of acute and chronic GvHD completely different. The rate of severe GvHD is markedly reduced in pediatric patients. This is important when developing optimal dosing or optimal timely scheduling of immunotherapy with the potential of inducing GvHD as this is the case in the current study using cytokine induced killer cells.

Consequently, knowledge obtained through the treatment of adult patients cannot be transferred to the treatment of pediatric patients. In addition, there is no gold standard treatment for patients, neither for children nor for adults with acute leukemia and MDS who are relapsing after allogeneic stem cell transplantation. So, there is a unmet need for developing strategies for rescuing these patients. The current treatment option with CIK cells is yet such an option for both, children and adults.

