## 1.5 Clinical Data

Based on our pre-clinical data, we analyzed safety and feasibility of a sequential, dose escalating administration of *in vitro* expanded CIK cells in patients with hematological malignancies after allogeneic SCT.

Our experience of repetitive, dose-escalating CIK cell infusions include 14 leukemia patients with risk of relapse (n=11) or overt relapse (n=3) showing no signs of acute GvHD >grade I after allogeneic SCT.

Between August 11, 2011 and November 30, 2014 14 patients (<18 years of age, n=13, median age 9, range 1-17 years; >18 years of age, n=1, age 69 years) with hematological malignancies (AML, n=7; ALL, n=6; CML, n=1) received a total of 58 CIK cell infusions (median number 3, range 1-10 per patient) from matched unrelated (n=6) or haploidentical (n=8) stem cell donors at a minimum of 3 weeks after allogeneic SCT and an interval of 4-6 weeks between infusions (median follow up after 1st CIK cell infusion 213 days, range 56-802 days). 6 patients received CIK cell infusions based on minimal residual disease or chimerism status, 5 patients, most of whom were not in remission at the time of allogeneic SCT, were treated prophylactically, and 3 relapsed patients received CIK cell infusions with or without chemotherapy.

Clinical batches of CIK cells were generated from peripheral blood mononuclear cells of the original stem cell donors under good manufacturing practice-conditions in the presence of interferon $\gamma$ , anti-CD3 antibody, interleukin (IL)-2 and IL-15. Cellular composition of CIK cell infusions showed that CD19+ B cells, CD14+ monocytes and CD3+CD56+ natural killer (NK) cells were quantitatively depleted while conventional CD3+CD56 T cells and CD3+CD56+ T-NK cells made up the bulk of the CIK cell product. T cells, evenly distributed between the CD4+ and CD8+ compartment, were activated, which was shown by CD25+ expression and were mostly TCR $\alpha/\beta$  type.

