#### Fluids

Large volumes of fluid may leak from the patient's circulation during an anaphylactic reaction. There will also be vasodilation, a low blood pressure and signs of shock. If there is intravenous access, infuse intravenous fluids immediately. Give a rapid IV fluid challenge (20 mL/kg in a child or 500-1000 mL in an adult) and monitor the response; give further doses as necessary. There is no evidence to support the use of colloids over crystalloids in this setting. Consider colloid infusion as a cause in a patient receiving a colloid at the time of onset of an anaphylactic reaction and stop the infusion. Hartmann's solution or 0.9% saline are suitable fluids for initial resuscitation. A large volume of fluid may be needed. If intravenous access is delayed or impossible, the intra-osseous route can be used for fluids or drugs when resuscitating children or adults, but only by healthcare workers who are accustomed to do so. Do not delay the administration of IM adrenaline attempting intra-osseous access.

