## **4 Study Population**

Acute leukemia and MDS patients aged >0 and <80 years of both gender experiencing molecular relapse after allogeneic stem cell transplantation.

It is known that the amount of leukemia cells is very critical for every type of immunotherapy. As a consequence, chemotherapy is needed to reduce the percentage of leukemia blast cells below 5%. And for this, patients need to be "eligible for chemotherapy" in terms of their general medical condition. Antineoplastic chemotherapy however, is necessary to bring patients, with frank hematological relapse after allogeneic stem cell transplantation, in complete hematological

remission (<5% of leukemia blasts in the bone marrow) before immunotherapy may be started.

All chemotherapy given for remission induction is not part of the study.

Chemotherapy has to be stopped 3 days before CIK cell infusions could be given.

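### Appendix 1 stages gut GvHD by fixed daily stool volumes at every body size, which can under-grade acute GvHD in smaller children

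*Protocol*

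**What the plan says.** Appendix 1 gives four volume bands for the gut: "Stage 0: No diarrhea, or diarrhea <500 mL/day", "Stage 1: Diarrhea 500-999 mL/day", "Stage 2: Diarrhea 1000-1499 mL/day" and "Stage 3: Diarrhea >1500 mL/day". Stage 4 rests on severe abdominal pain and not on volume. The grade table in the same appendix puts gut stage 1 under grade II, stages 2-3 under grade III and stages 2-4 under grade IV. The IBMTR index printed after it reuses the same gut stages.

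Section 3.2 refers all GvHD grading to Appendix 1. Section 4 admits "Acute leukemia and MDS patients aged >0 and <80 years of both gender", and Section 3.4 plans 20 children and 20 adults. Section 2.3 makes grade III/IV acute GvHD a primary endpoint. Sections 3 and 8.1 also use the acute GvHD grade in infusion decisions.

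**The concern.** Stool volume is the only organ item in the scale that depends on body size. Skin is staged as a share of body surface and liver as a bilirubin concentration. Elsewhere the protocol does adapt to size or age. Cell doses are per kg, Appendix 2 splits performance status at age 16, and the emergency guidance in Section 3.2 distinguishes children from adults: "Give a rapid IV fluid challenge (20 mL/kg in a child or 500-1000 mL in an adult". The gut item has no such adaptation.

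A volume that is moderate for an adult is very large for a toddler. A small child may therefore have to be much sicker, relative to size, to reach the same gut stage. This bears on the paediatric safety rate and on any comparison of children with adults. Section 1.2 already holds that "The rate of severe GvHD is markedly reduced in pediatric patients" and calls this important for dosing. A scale that leans the same way makes that belief harder to test.

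**Working it through.** **The plan's own figure.** Section 11 gives interval widths for n = 20. Exact (Clopper-Pearson) intervals with x = 20 × rate reproduce all 18 widths. For example, 4/20 gives 0.057 to 0.437, width 0.379 before the limits are rounded. The precision table is not in dispute.

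**Inputs.** The limits of 500, 1000 and 1500 mL/day come from Appendix 1. Body weights are not given, so 10 to 70 kg is assumed. This is plausible for the sponsor's earlier patients under 18 described in Section 1.5 ("median age 9, range 1-17 years").

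**Limits per kg.** Formula: limit ÷ weight. The ratio to a 70 kg adult is 70 ÷ weight.

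| Weight (kg) | Stage 1 from (mL/kg/day) | Stage 2 from | Stage 3 above | Ratio to 70 kg |
|---|---|---|---|---|
| 70 | 7.1 | 14.3 | 21.4 | 1.0 |
| 50 | 10.0 | 20.0 | 30.0 | 1.4 |
| 30 | 16.7 | 33.3 | 50.0 | 2.3 |
| 20 | 25.0 | 50.0 | 75.0 | 3.5 |
| 10 | 50.0 | 100.0 | 150.0 | 7.0 |

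**How many stages this could be.** This step assumes that output is proportional to weight. The scaled volumes illustrate the size of the gap and are not proposed cut-offs.

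- At 20 kg, the equivalent of an adult's 1000 mL/day is 1000 × 20/70 = 286 mL (70 kg reference) or 1000 × 20/50 = 400 mL (50 kg reference). Both fall below 500 mL and are stage 0 as printed.
- At 28 kg (an assumed weight for a child of about 9), the 70 kg reference scales the limits by 28/70 = 0.4 to 200/400/600 mL. Outputs of 400-499 mL are then stage 2 scaled but 0 printed, and outputs above 600 and up to 999 mL are stage 3 scaled but 1 printed. Between 200 and 1499 mL the gap is one or two stages.
- With the 50 kg reference the factor is 28/50 = 0.56 and the limits are 280/560/840 mL. From 280 to 1499 mL the gap runs from none (500-559 mL) to two stages (above 840 and up to 999 mL).

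**Effect on the endpoint.** With m missed events among 20 children, the reported rate is (x − m)/20. Each missed event therefore costs 1/20 = 5 percentage points. Two missed events equal the distance between the 0.20 and 0.10 rows of the Section 11 safety table. The documents give neither the children's weights nor the share of grade III/IV cases decided by the gut, so m cannot be estimated.

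**The case against.** The strongest reply is that the bias is assumed and not shown. No section says that stool output rises with body size, and weight-based fluids or cell doses say nothing about stool. This stands: the direction needs output to rise with size, and the per-kg ratios need it to be proportional. The fixed limits themselves are not in doubt.

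The second reply is that the gut is one of several routes to grade III/IV. Liver stages 2-4, skin, performance status and the pain-based gut stage 4 remain open. In Section 1.5, the three grade III cases among 14 patients had skin, gut and liver involvement together. This limits how often the grade would change, though not the direction. Section 3.2 also bars a further infusion under steroids or immunosuppression, so a child treated that way for gut GvHD is held back whatever the recorded stage.

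Three stronger readings are tempting, and the documents do not support them:

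- **That all 20 children are under-graded.** The ratio is only 1.4 at 50 kg and vanishes at 70 kg.
- **That the scale alone would produce the lower paediatric rate claimed in Section 1.2.** This would require knowing how often the gut decides the grade.
- **That a missed case changes the trial's conclusion.** The exact upper limit is 43.7% for 4/20 and 37.9% for 3/20, on either side of the 40% assumed for donor lymphocyte infusion. But 4/20 is an arbitrary example, and Section 11 calls the study explorative and attaches no decision rule to 40%.

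**Conclusion.** The point holds in limited form. Appendix 1 applies a size-dependent measure without adjustment to patients from infancy to old age, and that measure feeds a primary endpoint. The threshold for gut-driven grade III is 2.3 times higher per kg at 30 kg than at 70 kg, 3.5 times at 20 kg and 7 times at 10 kg.

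If stool output rises with body size, grade III/IV acute GvHD is under-graded in smaller children whose gut stage decides the grade. The child-adult contrast is then partly confounded by the scale. The loss is 5 percentage points per missed event, with the number of events unknown. No sample size or interval width in Section 11 changes. Because the remedy is simple and only part of the paediatric group is affected, this is a cheap improvement.

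**What to change.** - The sponsor's clinical lead should reconcile Appendix 1 with the paediatric population by adopting a size-adjusted paediatric gut staging. No cut-offs are proposed here. Because the grade also enters infusion decisions, the amendment should state where each staging applies.
- Record daily stool volume at each GvHD assessment. The schedule of assessments lists GvHD grading and body weight (at screening and at 2-4 weeks after infusion) but not stool volume. A volume that was never recorded cannot be restaged later.
- Report the paediatric grade III/IV acute GvHD rate under both the printed and the size-adjusted staging, so that the influence of the scale is visible.

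The cost is one CRF field and a protocol amendment, which under Section 7.7 needs ethics committee and authority approval if it is substantial. The paediatric GvHD rate may come out higher.
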